### Outcomes and data collection

The primary outcome is HIV-related knowledge; the secondary outcomes comprise HIV-related stigma attitude, HIV-related behaviors attitude, and HIV-related behaviors. The assessment will be conducted in 2 weeks and 1, 3, and 6 months after the second intervention. At the same time, the acceptability and the method to acquire relating knowledge of HIV prevention will be also evaluated after 2 weeks.

HIV-related knowledge will be assessed through a questionnaire. The item of the questionnaire is designed according to the part of the contents for older people in the Core Knowledge of AIDS Prevention And Control Publicity And Education [24] issued by Chinese CDC. There are 10 items in total, one point for a correct answer. The higher the score means the more knowledgeable participants have learned. Six experts were invited to verify the content validity of this questionnaire. The results showed that the item-level CVI (I-CVI) and the scale-level CVI (S-CVI) were both 1.000.

HIV-related stigma attitude will be assessed through the Chinese version of Zelaya’s HIV/AIDS Stigma Scale, which was firstly compiled by Zelaya [25]. The scale, which included 24 items in total, was sinicized by Xing Haiyan in 2014 [26]. In the Chinese version of Zelaya AIDS Discrimination Scale, the Cronbach’s *α* coefficient of the scale was 0.91, and the Cronbach’s *α* coefficient of each dimension was 0.79–0.87. It consisted of four dimensions (fear of infection, stigma prejudice, personal discrimination, social discrimination), with six items for each dimension, a total of 24 items. There were 18 negative items and 6 positive items, and the answers were strongly agree, agree, uncertain, oppose, and strongly disagree. Six positive items are recorded as 1, 2, 3, 4, and 5 points in turn, while 18 negative ones are the opposite. The higher the score of discriminatory attitude, the more serious AIDS discrimination.

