### Statistical analyses

All questionnaires will be administered at baseline, and the final analyses will be adjusted for the baseline scores. Descriptive statistics will be used to show the baseline characteristics of each arm. The outcome measure (HIV-related knowledge, HIV-related behaviors attitude, and HIV-related behaviors) is a binary variable, and it will be compared by chi-square tests among the three arms at 2 weeks later and 1, 3, and 6 months of follow-up. To measure the HIV-related stigma attitude outcome, analysis of variance (ANOVA) will be used to find out whether there are differences among the three arms after 2 weeks of intervention. Repeated measures ANOVA will be used to measure the HIV-related stigma attitude score at 1, 3, and 6 months of follow-up. A Bonferroni correction will be used for multiple testing. Intention-to-treat analysis will be used to account for the influence of attrition. *P* ≤ 0.05 will be deemed statistically significant. All analyses will be performed using SPSS software.

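### The tests named for stigma carry no baseline covariate although baseline adjustment is promised, and the 2-week visit is left out of the longitudinal model

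*Protocol article*

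**What the plan says.** Three statements in Statistical analyses bear on stigma.

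- A general promise: "All questionnaires will be administered at baseline, and the final analyses will be adjusted for the baseline scores".
- For the first follow-up: "analysis of variance (ANOVA) will be used to find out whether there are differences among the three arms after 2 weeks of intervention".
- For the later follow-ups: "Repeated measures ANOVA will be used to measure the HIV-related stigma attitude score at 1, 3, and 6 months of follow-up".

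The section sets the significance threshold ("0.05 will be deemed statistically significant") and adds "A Bonferroni correction will be used for multiple testing", without saying which tests form the family. It does not say which term of the repeated-measures ANOVA (arm, time or arm-by-time) answers the hypothesis.

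Table 3 schedules the stigma scale at baseline and at all four follow-ups, and Outcomes and data collection agrees on the follow-up times: "The assessment will be conducted in 2 weeks and 1, 3, and 6 months after the second intervention". That section makes stigma secondary: "the secondary outcomes comprise HIV-related stigma attitude, HIV-related behaviors attitude, and HIV-related behaviors". Aim/objectives nevertheless lists stigma reduction among the primary objectives, and the first hypothesis in Methods/design predicts less stigma in the Sunset arm than in the control arms.

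**The concern.** The general promise and the named procedures do not match. An ANOVA at one visit, and a repeated-measures ANOVA on three later visits, contain no baseline score unless it is added as a covariate. An analyst who runs exactly what is named would not deliver the adjustment, and would give up the precision that a correlated baseline score provides.

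Separately, the longitudinal model begins at 1 month. The visit closest to the intervention gets its own test, and no single model describes the course of the arm differences from 2 weeks to 6 months. The result is two partial answers to one between-arm question, with no stated rule for which term or contrast decides it.

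**Working it through.** **The plan's own figure.** Sample size and adherence gives 135 per group for 80% power on knowledge, raised to 150. No effect size, SD or rates are given, so 135 cannot be reproduced. The step to 150 does reproduce with 10% attrition: 135 / 0.9 = 150. Solving backwards at two-sided 0.05, 135 per group detects (1.960 + 0.842) × √(2/135) = 0.341 SD. The point does not rest on these figures. They only supply n = 135 and a plausible effect size.

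**Assumptions not in the documents.** One arm differs from the other two by d SD, and the other two are equal. Any two visits have the same correlation r. Data are complete. The omnibus three-arm F test is run at 0.05 with no Bonferroni correction.

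**Formula.** With arm means d, 0, 0, the squared deviations from their mean sum to (2/3)d². The noncentrality is therefore λ = n·d²·(2/3)/v, with 2 numerator df and 402 denominator df (401 with a covariate). The variance v is:

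- 2 weeks, no covariate: 1
- 2 weeks, with baseline: 1 − r²
- mean of k visits, no covariate: (1 + (k−1)r)/k
- mean of k visits, with baseline: (1 + (k−1)r)/k − r²

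**Cost of omitting the covariate** (d = 0.3, n = 135, so λ = 135 × 0.09 × 2/3 / v = 8.1/v):

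| r | 2 weeks, no baseline | 2 weeks, with baseline | 1/3/6-month arm effect, no baseline | 1/3/6-month arm effect, with baseline |
|---|---|---|---|---|
| 0.5 | 72.0% | 84.3% | 88.5% | 98.2% |
| 0.6 | 72.0% | 89.8% | 85.1% | 99.0% |
| 0.7 | 72.0% | 95.4% | 81.7% | 99.7% |

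For example, at r = 0.6 and 2 weeks with baseline, v = 1 − 0.36 = 0.64, λ = 12.66 and power is 89.8%.

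**Cost of the split once baseline is adjusted for, constant effect.** At d = 0.3 and r = 0.6, v is 0.373 for three visits and 0.340 for four, giving 99.0% against 99.5%. At d = 0.2, λ = 3.6/v:

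| r | three visits | four visits |
|---|---|---|
| 0.5 | 74.9% | 79.5% |
| 0.6 | 79.7% | 83.5% |
| 0.7 | 86.9% | 89.7% |

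**Fading effect.** Take 0.341, 0.25, 0.12 and 0 SD at 2 weeks, 1, 3 and 6 months. The mean effect is 0.37/3 = 0.123 SD over the last three visits and 0.711/4 = 0.178 SD over all four. Simulation (2,000 runs per setting; r = 0.3, 0.5, 0.7) gives:

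- arm effect over 1, 3 and 6 months, no baseline: 28%, 24%, 20%
- the same with baseline: 34%, 36%, 45%
- arm effect over all four visits with baseline: 69%, 69%, 81%
- the separate 2-week ANOVA, no baseline: about 83% throughout

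**Which term is read.** For a constant 0.341 SD effect at the same three correlations, the arm-by-time term over 1, 3 and 6 months rejects in 4.0%, 4.8% and 4.6% of runs, which is its false-positive rate. The arm main effect in the same model rejects in 98.5%, 95.6% and 90.4% without baseline, and in at least 99.5% with it.

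**The case against.** The strongest reply is that baseline is not absent from the plan: "the final analyses will be adjusted for the baseline scores" covers every outcome, and a condensed article may write ANOVA where an adjusted analysis is meant. That stands in part. The power loss in the first table arises only if the named tests are run without the promised covariate. It would be wrong to infer that the plan has decided to discard baseline.

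A reader might also infer that a lasting stigma effect would be reported as null, because arm-by-time cannot show it in a model that starts at 1 month. The documents do not support this. They never name arm-by-time as the test, the hypothesis is a difference between arms, and the arm main effect finds a lasting effect readily. The arm-by-visit term of the mixed model proposed below would also be null for a constant effect, so this property is not peculiar to the split.

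Finally, testing the immediate effect separately from its durability is a legitimate choice, and the 2-week visit does have its own test. That also stands, and for a fading effect that test recovers much of what the later model loses. What remains is that the named tests do not carry the promised adjustment, and that the later model cannot estimate change from 2 weeks onward.

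**Conclusion.** The point holds in limited form. The promised adjustment and the named stigma tests need to be reconciled, and the longitudinal model should include the 2-week visit.

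The larger loss is conditional. Without the covariate, 2-week power falls short of the adjusted analysis by 12 to 23 percentage points (84.3 − 72.0 and 95.4 − 72.0, for 0.3 SD and correlation 0.5 to 0.7). With the covariate, the split costs about 3 to 5 points for a constant 0.2 SD effect. It costs more for a fading one, although the separate 2-week test partly offsets that.

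All these figures rest on assumed effects and correlations, equal correlation between visits, complete data with 135 men per arm, and no multiplicity correction. Stigma is secondary, so this is an improvement worth making and not a flaw that endangers the primary comparison.

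**What to change.** Replace both stigma tests with one linear mixed model (available in SPSS) on the score at 2 weeks, 1, 3 and 6 months. Fixed effects are baseline stigma score, arm, visit and arm-by-visit, with unstructured covariance within each man.

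Name the baseline-adjusted Sunset-minus-normal-video and Sunset-minus-lecture differences at each visit, with 95% intervals, as the test of the hypothesis. Say explicitly that the arm-by-visit term is not that test. This gives 2 × 4 = 8 contrasts, so state which of them the Bonferroni correction covers.

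The cost is a change of wording in the analysis section. The data, visits and software stay the same.

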## Methods/design

Four hundred and fifty participants will be allocated to one of the three randomized groups after completing a baseline survey. Baseline assessments last approximately 30 min and include demographic items, HIV-related knowledge items, HIV-related stigma attitude items, HIV-related behaviors attitude items, and HIV-related behaviors items. At the same time, the acceptability and the method to acquire relating knowledge of HIV prevention will be evaluated through face-to-face interviews with participants.

To reduce contamination, the three groups will be from separate areas. Four follow-up visit assessments are expected at 2 weeks later, 1 month, 3 months, and 6 months. Our hypotheses are as follows: (1) compared with older men in the control groups, those in the *Sunset Without AIDS* intervention group will have a deeper awareness of HIV, less HIV-related stigma, and fewer HIV-related risk behaviors; (2) in comparison between the *Sunset Without AIDS* intervention group and normal video group, the former group integrated various knowledge and behavioral skills into the story. So, it will have better acceptability and feasibility on HIV prevention. Figure 4 shows the study flowchart.

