### Sample size and adherence

The sample size calculation is based on the primary outcome, i.e., HIV-related knowledge. The sufficient statistical power to detect changes in HIV-related knowledge after the intervention were considered in sample size calculation, and 135 participants were need in each group to maintain 80% statistical power. Considering this sample size was also powered for the secondary outcomes and the attrition rate, the sample size of each group was determined to be 150, and the total sample size was 450.To motivate participants to stay in the trial, we would use intrinsic reward to help 450 participants adhere to the intervention and follow-up. Participants would receive some prizes for each assessment. In addition, after completing the research, each participant would also receive a reward of 50 RMB in cash.

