### Randomization and allocation concealment

Individual randomization will be used in allocation. Participants will be randomly assigned to one of the three intervention groups on a 1:1:1 basis. Opaque envelopes will be prepared for randomization. In 450 envelopes, each will contain a note with the words “*Sunset Without AIDS* intervention group” or “Normal video group” or “Lecture group” (150 envelopes per group). A statistician will be responsible for the generation of random sequence numbers and place them on a sequential list that will be maintained by the trial coordinator. Participants (*n* = 450) will be randomly assigned a computer-generated random number from 1 to 450, and they will randomly select an envelope in the numbering order. For each envelope selected by participants, the total number of envelopes will be reduced by one until all 450 are achieved. Participants will be randomly allocated to the different groups with a closed envelope and supervise from a third party. Separate research staff will record the allocation information of the participants. Another staff will assign participants to interventions. These staff members were not involved in the data collection and analysis process. The data analysts are blinded to the allocation. All interviewers are not involved in delivering the intervention, so they will also remain blinded.

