### Contamination and intervention fidelity

To help ensure intervention fidelity and reduce contamination, we developed and revised multiple strategies. Some of the key strategies are listed in Table 2.

**Table 2 Tab2:** Key strategies to ensure intervention fidelity and reduce contamination

- Increased sample size up to 10% - The study group will discuss the types, scope and measures of reducing possible contamination sources through discussion and literature review - Training of trial staff and health workers to emphasize the effects of contamination. How to avoid it, how to use unbiased explanations to solve the problem - Different intervention groups will be delivered in separate areas - Intervention videos are kept by designated personnel and not available through other channels - Information packs with *Sunset Without AIDS* materials are clearly labeled and stored separately from normal video groups’ materials - Level and extent of participants reported contamination are measured at follow-up visits - Participants will be escorted before grouping and between survey locations - Field study team members confirm that trial participants only receive the specified intervention - Participants are randomly assigned to different groups by selecting envelopes - The data analysts are blinded to the allocation - Ensure that the educational content and duration of the video downloaded from the website of the Chinese CDC is the same as that of *Sunset Without AIDS* - Lecture group will be conduct by an AIDS expert for the same amount of time and content as the intervention group - Intervention sessions audio recorded, and 10% reviewed centrally [23] - All trial investigators will remain blinded	

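### Single-step Bonferroni is valid here, but Holm's step-down procedure gives the same familywise guarantee and more power to show that Sunset beats both control groups

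*Protocol article*

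**What the plan says.** In the protocol article, the Statistical analyses section names the method outright: "A Bonferroni correction will be used for multiple testing". The significance rule is that P at or below "0.05 will be deemed statistically significant". No step-down version, hierarchy or reason for the single-step form is given.

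The hypotheses under Methods/design are framed against more than one comparator: "compared with older men in the control groups, those in the" Sunset arm are expected to do better. The Discussion then draws one conclusion from Sunset against the normal video and a separate one from Sunset against the lecture.

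On size, Sample size and adherence says "135 participants were need in each group to maintain 80% statistical power", and after allowances "the sample size of each group was determined to be 150, and the total sample size was 450". Allocation is equal: "Participants will be randomly assigned to one of the three intervention groups on a 1:1:1 basis".

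**The concern.** Bonferroni compares every P value in a family of m tests with 0.05/m. Holm compares the smallest with 0.05/m, the next with 0.05/(m−1), and so on up to 0.05, stopping at the first non-rejection. Both control the probability of any false rejection at 0.05 whatever the dependence between tests. Each Holm threshold is at least as large as Bonferroni's, so Holm can never reject less. This holds for chi-square tests and ANOVA alike, and for any family.

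The advantage arises only after a first rejection, and this trial's conclusions need a second one, because Sunset is to be judged against two active controls of the same duration and similar content. With the sample fixed at 450, the choice of procedure determines how often a real benefit over both controls is established.

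**Working it through.** **Inputs from the article.** 135 per arm for 80% power and 150 per arm recruited (Sample size and adherence); three arms at 1:1:1 (Randomization and allocation concealment); significance level 0.05 (Statistical analyses).

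**Assumed.** Two-sided tests, a normal approximation and equal effects against both controls. No effect size, standard deviation or rate is given; the text says only that "The sufficient statistical power to detect changes in HIV-related knowledge after the intervention were considered in sample size calculation".

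**The plan's own figure.** Without an effect size, 135 cannot be reproduced. The step to 150 is consistent with a 10% loss: 135/(1 − 0.10) = 150. Table 2 also lists "Increased sample size up to 10" per cent. Working backwards from 135 instead, the standardised difference that gives 80% power is

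d = (z for alpha/2 + z for 80%) × √(2/n) = (1.960 + 0.842) × √(2/135) = 0.341 at alpha 0.05.

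If 135 already allowed for a correction, d would be 0.375 (alpha 0.025) or 0.394 (alpha 0.05/3).

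**Correlation of the two contrasts.** Both use the Sunset mean. With equal arms the covariance is σ²/n and each variance is 2σ²/n, so the correlation is 0.5.

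**Decision rules for two contrasts.** Bonferroni declares both when both P ≤ 0.025. Holm declares both when the smaller P ≤ 0.025 and the larger P ≤ 0.05.

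**Power to show Sunset better than both controls** (2,000,000 simulated three-arm trials):

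| Family | n per arm | d | Bonferroni | Holm | Gain (points) |
|---|---|---|---|---|---|
| Two contrasts | 135 | 0.341 | 57.2% | 67.7% | 10.5 |
| Two contrasts | 135 | 0.375 | 68.8% | 77.9% | 9.1 |
| Two contrasts | 150 | 0.341 | 63.6% | 73.4% | 9.8 |
| Two contrasts | 150 | 0.394 | 80.1% | 87.0% | 6.9 |
| Three pairwise | 135 | 0.341 | 50.6% | 57.1% | 6.5 |
| Three pairwise | 150 | 0.394 | 75.1% | 80.2% | 5.1 |

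In the first row, both P values are at or below 0.05 in 68.8% of trials. Holm misses only those in which both lie between 0.025 and 0.05: 68.8 − 67.7 = about 1.1%. Bonferroni also misses those in which one P is at or below 0.025 and the other lies between 0.025 and 0.05: 67.7 − 57.2 = 10.5%.

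**Other results for two contrasts, n = 135, d = 0.341.**
- Power for one given contrast: 71.2% with Bonferroni, 76.5% with Holm.
- At least one rejection: 85.3% with either method, since the smallest P meets the same threshold.
- Trials in which Bonferroni declared both contrasts and Holm did not: none.
- Bonferroni needs about 161 per arm to match Holm at 135 (67.5% at 160, 69.3% at 165).

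**Familywise error.**
- Both nulls true: 0.046 for each method.
- One null true: 0.025 for Bonferroni and 0.041 for Holm, rising to 0.050 for Holm when the other effect is very large. All are within 0.05.

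**Dependence on correlation** (two contrasts, 80% power each). Holm's gain for both contrasts is 12.6 points at correlation 0, 11.5 at 0.25, 10.5 at 0.5, 9.2 at 0.75 and 7.7 at 0.9.

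**The case against.** The strongest reply is that nothing is wrong: Bonferroni controls the error rate, and a more powerful alternative is optional. That stands, and it limits the point to efficiency. It does not remove it, because the method is positively named and the alternative has the same guarantee.

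The family is not declared in this article, and the tests described are three-arm comparisons, so the two-contrast figures are not the only reading. This also stands. It is why the smaller three-pairwise gain is given beside them. The direction is the same for any family; only the amount changes.

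If success required beating both controls, each contrast could be tested at 0.05 without adjustment (68.8%, against 67.7% for Holm). That is correct, but the article does not define success so, and it interprets the two comparisons separately.

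Holm is not free. With one of two nulls true it uses more of the permitted 0.05, and Bonferroni gives simultaneous intervals that match its decisions. Both stand as costs.

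Three stronger readings are tempting and unsupported. A reader might infer that positive correlation, from the shared arm or repeated visits, is what makes Bonferroni costly here; with two contrasts the gain shrinks as correlation rises. A reader might multiply contrasts by visits and ask for significance on every one; the article sets no such criterion. A reader might infer that the trial is underpowered; the article does not say whether 135 per arm already allows for the correction, and if it does a shortfall is not shown.

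**Conclusion.** The point holds as a cheap improvement. Single-step Bonferroni is valid but gives up power on the second and later comparisons, where the article wants conclusions. If each contrast alone has 80% power at two-sided 0.05, the loss in power to beat both controls is about 10 points for two contrasts (57% against 68%) and about 6 points for three pairwise comparisons (51% against 57%). Over the effect sizes and arm sizes examined, the ranges are about 7 to 10.5 and about 5 to 6.5 points. These sizes rest on an assumed effect, equal against both controls, and on a normal approximation. That Holm is never weaker rests on none of these. The chance of winning against at least one control is unaffected, and no conclusion reached under Bonferroni would be invalid.

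**What to change.** Replace the Bonferroni sentence with: multiplicity is controlled by Holm's step-down procedure at overall two-sided 0.05 over the declared family of m tests; ordered P values are compared with 0.05/m, 0.05/(m−1), …, 0.05, stopping at the first non-rejection. Report Holm-adjusted P values, so that the existing 0.05 rule applies to them directly. The adjusted value for the j-th smallest P is the largest of (m − i + 1) × P(i) over i ≤ j, capped at 1.

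If simultaneous intervals are wanted, keep them at Bonferroni width and state that an interval may include no difference where the Holm test rejects.

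The cost is one sentence and a small calculation on the SPSS P values, with no extra participants or data. The change should be made before outcomes are compared by arm. If the investigators regard it as an important modification, it goes to the ethics committee and the registry, as Ethical considerations already provides.
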